## Abstract

Obtaining a stool specimen for diagnostic testing of enteric conditions (e.g., gastroenteritis) can be a challenging and unpleasant experience. A person is required to obtain a sample pot from a healthcare location, return home and wait until they have a bowel motion, and then deal with the challenges of returning the sample to the clinic or pathology centre. This trial aims to identify whether the simpler approach of obtaining a rectal swab is effective for diagnosing enteric conditions. Recruitment will take place in a variety of settings, including suspected norovirus clusters, Hepatitis A clusters, in both hospital, and community settings. We will compare paired stool and rectal swab sample polymerase chain reaction (PCR) testing to determine whether rectal swabs are a reliable proxy for faecal sampling. Persons who would normally be provided with a faecal specimen container, will also be provided with a rectal swab for self-collection or clinician-collection (within 24 hours of the bulk faeces collection). We will assess the sensitivity, specificity, positive predictive value, negative predictive value using standard confusion matrix. The gold standard reference will be considered the bulk faeces PCR tests. We hypothesise that rectal swab PCR testing will be equally as effective as bulk faeces PCR testing. If successful, rectal swab PCR testing could be implemented as routine practice with several key benefits. Firstly, it would improve the patient experience by conveniently enabling stool collection at the point of care, which is rarely possible currently. Secondly, it would reduce healthcare costs, and streamline collection processes by eliminating the need for persons to return to a clinic to deliver specimen. Thirdly, the ease of testing will likely increase testing rates and compliance, leading to better diagnoses and more accurate clinical care. The protocol described has the potential to revolutionise daily clinical practice.

**Trial registration**: Australian New Zealand Clinical Trials Registry (ANZCTR): ACTRN12624000095561.

## Introduction

Testing persons with gastroenteritis-like illnesses necessitates the provision of a faecal sample. This method is not without drawbacks; in particular, the very nature of defecation means that samples cannot be provided ‘on demand’ in a physician’s office or to a research nurse and are reliant on appropriate collection by patients themselves [1]. Patients in hospitals with diarrhoea commonly use the toilet before healthcare workers can take a stool sample. Faeces sampling may also present additional complexities, including the logistical challenges of having to transport samples between the patient’s home, the clinic and the laboratory, and considerable patient reluctance to providing samples. Rectal swabbing has been shown to be a valid alternative in several research and clinical settings [2,3].

Rectal swabbing is standard practice in Australia and overseas for the surveillance and screening of multi-resistant organisms. National U.K and Australian guidance mandates the use of rectal swabs for screening for intestinal colonisation with carbapenemase-producing Enterobacteriaceae for at-risk patients admitted to healthcare settings [3,4]. The key benefits of rectal swabs include the ease with which they can be administered and transported, and the high levels of acceptability to patients/research study participants [3].

Self-collection as a process has been shown to be an accurate testing methodology in other settings. Human papilloma virus self-collection has been shown to be just as accurate, or even more sensitive than clinician collected samples [5–7]. The accuracy of rectal swabs vs bulk faeces testing has been tested extensively using culture mediums, but although some research has been done in this area since the advent of polymerase chain reaction (PCR) testing methodology, routine use has not been adopted.

Studies have long compared rectal swabs vs bulk faeces testing. The results are varied, depending on the year the study was performed. An early study examining 700 specimens tested with MacConkey’s medium in 1940 during a Sonne dysentery outbreak (*Shigella sonnei* sp. outbreak) found that rectal swabbing was far superior to bulk faeces culture to detect an organism [8]. Rectal swabbing became the standard for a period of time This was disputed later in 1954 after a group examined 3,183 index cases looking for a variety of organisms to which they concluded that the *“…626 [bulk faeces] specimens all showed abnormalities which could be demonstrated only by microscopy or simple chemical methods, for which the rectal swab is quite unsuitable”* [9]. Since then, huge changes have occurred to our detection methods (e.g., culture media) and the advent of PCR testing for multiple organisms at once.

More recent studies demonstrate that the differences between rectal swabs and faecal samples is driven by the type of test (bacterial microscopy and culture vs viral PCR). A phase I clinical study for a live oral attenuated *Salmonella* Typhi vaccine strain found that when compared with faecal culture, rectal swabs were 64% sensitive and 90% specific [10]. A recent study on paired samples found that for bacteria, the sensitivity was 86.5% (95% CI 79.5%, 91.8%) when PCR was performed and 61.4% (95% CI 52.4%, 69.9%) when culture for bacteria was performed, indicating better performance for PCR [11].

It has been shown in small studies that rectal swabs are likely accurate. Studies have now shown that during testing for various enteric organisms (viruses and bacteria) in Rwandan children there was no significant difference in detection rate between faeces and rectal swabs for any agent, reflecting that pathogen concentration was far above the limit of detection in the majority of cases [12]. A similar paired sample study focusing on norovirus found a sensitivity of rectal swabs that was greater than 97%, and in one case detected norovirus in the swab, but not in the bulk faeces [13].

The outcome of this project will transform clinical practice for doctors and patients. It will make testing far more convenient and allow for point-of-care testing to become a reality for enteric organisms. Currently, many people leave the emergency department without a faecal test because they could not produce a specimen while they were with the clinician. Rectal swabbing would make the diagnosis, and better care available for these patients. Public Health practitioners would be able to perform mass testing after small or large scale outbreaks, such as those caused by hepatitis A, norovirus or other organisms found in faeces [14,15]. Doctor’s in the emergency department would be able to obtain swabs on demand for testing that would expedite time spent in ED and, with the earlier diagnosis, length of stay in hospital. Most importantly, for patients, it means that they no longer must go home, wait until they need to have a bowel motion, and then return to the hospital or GP clinic with their sample, as it can be done on demand, on-site (in a private situation). Thus, rectal swabbing can transform clinical practice through earlier diagnosis, shorter length of stay’s and greatly improving the patient experience. This study aims to demonstrate that self-collected or clinician collected rectal swabs are a valid alternative method of testing when compared to bulk faeces testing for a wide range of enteric organisms such as bacterial, viral, and parasitic/protozoan. The intended outcome of this project is to replace bulk faeces testing with rectal swabbing in daily clinical and public health practice.

## Methods

This is a single group paired sampling prospective trial comparing the diagnostic accuracy between an established method and an alternative method of diagnosis. Participants of the study are required to use both sampling methods to allow for comparison of results. A broad timeline of the trial is presented in Fig 1. This trial was registered with the Australian New Zealand Clinical Trials Registry (ANZCTR) (registration number: ACTRN12624000095561) on 02/02/2024. Ethics approval was granted for this trial by the Metro North Human Research Ethics Committee (HREC) (EC00168) on 19/12/2023. Written or verbal consent to participate will be obtained from each participant. Records of consent will be stored securely.

**Fig 1 pone.0329643.g001:**
[figure not shown]
SPIRIT schedule. SPIRIT schedule of enrolment, interventions, and assessments.

### Study setting

The study aims to recruit patients in the community (primary care or public health responses) and in public hospitals. The mode of collection will either be a self-collect rectal swab (done by the patient themselves) and bulk faeces sample or clinician collect rectal swab and bulk faeces sample within a clinical environment. The generalisability of this trial is supported by its relatively broad inclusion and exclusion criteria, which are designed to reflect routine clinical practice. Because the trial aims to evaluate the use of rectal swabs as an alternative to bulk faeces sampling, eligibility is not restricted (e.g., based on symptom presentation), allowing for the inclusion of participants with diverse clinical profiles. This inclusive approach will mimic routine clinical practice, and facilitate recruitment across a broad range of demographic, clinical, and socioeconomic backgrounds, enhancing the external validity of the findings. Vulnerable groups, such as comorbid or immunocompromised individuals, are identified in the recruitment phase and this data is recorded to be used in the analyses. The lower age limit of 18 years has been set due to ethical and regulatory considerations in recruiting children and performing rectal swabs on a vulnerable group. While children are not included in this study, the trial findings relevant to rectal swab accuracy are expected to be applicable to all ages.

Inclusion criteria:

Persons aged 18 and older.Able to consent to and perform the additional rectal swab test.Close contact or person exposed, suspected, or confirmed case associated with an outbreak of an enteric organism. E.g., hepatitis A outbreak, foodborne outbreak.Chronic carrier of an enteric organism that requires testing.Person involved in a clinical encounter where they are or are likely suffering from a disease caused by an enteric organism. (E.g., person presenting to the GP or Emergency Department with diarrhoea or jaundice)

Exclusion criteria:

Persons unlikely (as judged by the clinician) to be harbouring an enteric organism.Persons where collection of a rectal swab is medically contra-indicated.

### Consent

In all study settings, the potential participant will be asked by the treating clinician for consent to be contacted by the local study coordinator. After which the local study coordinator/study nurse will contact the person to obtain consent for inclusion into the study.

There will be two ways that a participant can consent to participating (verbal, written). Verbal consent will be obtained over the phone with a study coordinator or study nurse, as is commonly done in outbreak situations. The study nurse will read the patient information sheet to the participant over the phone, ensure the participant understands the process and document this in a database held on Queensland Health data servers. The testing pack will be sent to the participant and will include the patient information sheet about the study and all contact details for questions about the study. Furthermore, implicit consent will occur when the participant obtains both samples (the participant can decline to participate by not providing the rectal swab) and returns one or both samples to the pathology laboratory.

If the testing is done in person (a study clinician is present), verbal, written and implicit consent (the patient will obtain the sample themselves and return it to the study coordinator) will be obtained using the patient information sheet, and the signature document will be kept, with a copy offered to the participant.

Opting out of the study will be possible for participants at all stages of the study, up until the analysis of the research. For example, a participant may agree to participation over the phone, then, once they receive the full pack with the Patient Information Sheet, and they read over it in detail, they can withdraw from the study by calling us and withdrawing, or, not sending the rectal swab, and then withdrawing after we check in with them after the rectal swab was not returned.

### Risks and harm

Risks associated with the rectal swab sample collection process include discomfort or pain, and in rare cases, infection. In some cases, participants may experience minimal bleeding. There is a low to medium risk of these events occurring if sample collection is conducted properly. These risks are outlined in the patient information and consent form, ensuring that participants are fully informed prior to their involvement. To mitigate these risks, strict adherence to hygiene and sterile techniques is emphasized during both self-collection and clinician-guided collection.

### Trial process

The site study coordinator will provide participants with oral and written information about the procedure, including its purpose, what to expect (2 tests being performed), and potential risks and then obtain verbal or written informed consent. The participant will ensure all necessary materials are present in the pre-prepared packs which will include sterile rectal swabs, bulk faeces collection sample container, gloves, pre-filled pathology form and labeling supplies. The participant or clinician will conduct the procedure in a private, clean, and comfortable setting to maintain participant dignity and comfort (preferably a toilet).

#### Collection process.

Participants are encouraged to perform thorough hand hygiene before and after the procedure and wear the disposable gloves provided in the packs to maintain sterility and prevent contamination. Ideally the participant will swab first and then provide a bulk faeces sample second. The swab will be gently inserted into the rectum, approximately 2–3 cm (about 1 inch). The swab should be rotated for 10–15 seconds to ensure adequate sampling. The swab should be carefully withdrawn, ensuring not to touch any external surfaces to avoid contamination. The participant will defecate directly onto a paper or plastic liner or into the collection device. The participant will be informed not to urinate at the same time to avoid contaminating the sample. Using the provided scoop or spatula, the participant will then transfer a portion of the faeces into the provided collection container. A sample size of approximately 5 grams (about the size of a walnut) should be collected. The containers (rectal swab and bulk faeces) should be securely sealed to prevent leakage. Containers will be properly labelled with the participant’s unique identifier, date, and time of collection.

#### Control sample (bulk faeces).

The bulk faeces sample is used as the control sample in this study as this sample type is currently used in routine clinical practice. In this context, bulk faeces PCR testing is considered the gold standard. It is acknowledged that bulk faces PCR testing may be associated with technical or interoperability limitations. To minimise the uncertainty that this could pose on testing results, paired samples that do not produce the same results will be managed internally according to laboratory protocol.

#### Sample handling, transport and storage.

After the sample has been properly labelled, the sample will be transported to the laboratory as soon as possible to maintain sample integrity. The sample may be stored in a refrigerator until it can be sent to the lab and/or processed. A clear chain of custody for the sample will be maintained, documenting each step from collection to laboratory analysis.

#### Follow-up.

Each person will receive a follow-up phone call after the test has been completed. The participant will be asked structured questions regarding the testing procedure:

“Which sample did you collect first?” (bulk/swab). This will help to validate the timing of sample collection, ensuring that samples that were collected close together (e.g., the participant records the same collection time for the swab and container) in time can be ordered.“Did you experience an adverse event during or after collecting the swab sample? (yes/no). If so, what was the nature of the event?” (qualitative). The adverse event will then be classified according to classification definitions described in ‘adverse event reporting and harms’.“Which test did you prefer?” (bulk/swab). “Why?” (qualitative)

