### Timeline

Participant recruitment is expected to commence in early 2025. Recruitment and data collection are expected to be completed within two years. Results are expected shortly after, placing the trial completion date in late 2027 or early 2028. It is expected that an average of 3–6 swabs will be obtained per week across collection sites. Some situations, such as outbreaks or mass gathering events, will allow for greater numbers of swabs to be collected in a small timeframe. After participants return the test samples, they will receive a follow-up phone call. Results of the bulk faeces test will be returned to the patient by the clinician that requested the test.

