#### Missing data.

To minimise occurrences of missing data, the data collection tool will be designed in a clear and easy-to-operate format. Any members of the research team who may be responsible for data collection and data input will be familiarised with data collection/storage tools and processes, which will ultimately reduce occurrences of missing data due to an avoidable error. Minimum data requirements are defined within the data collection platform to ensure instances of missing data are easily identifiable and can be followed up promptly (e.g., missing symptomatology details).

Data relevant to consent, participant identifiers and dual samples must be reported at the bare minimum. We will require each site to monitor and report missing data every 6 months. If a participant withdraws from the study after providing consent, the reason for withdrawal will be recorded and taken into account in data analysis and interpretation stages. Non-critical missing data will be managed via sensitivity analyses, and if amenable, multiple imputation will be used. In the event that a participant does not return the swab (critical data), that participant will be contacted to check if they wish to withdraw from the study. If the individual wishes to remain part of the study, they will be supported to provide the additional sample (e.g., required sample kit will be provided again if necessary). Participants will be encouraged to supply the bulk faeces sample at a minimum to complete routine clinical or public health care. If the participant withdraws from the study, or is unable to be contacted, the participant’s data will be omitted.

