#### Decision rules.

Stopping for Safety: Predefined criteria for stopping the trial if a significant safety concern are identified; for instance, if the incidence of severe adverse events is above what is expected.Stopping for Efficacy: Criteria for stopping the trial early if rectal swabs show clear and overwhelming evidence of inferiority, based on predefined statistical thresholds and thus it is futile to continue. A cutoff of 0.35 difference in accuracy for inferiority with an alpha of 0.05 at interim analyses will be used to support decisions on continuing, modifying, or stopping the trial. As this is a diagnostic test trial, the decision to stop the trial must be multifactorial in nature and made by the Trial Steering Committee.

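### The only adverse event question described follows test completion, and participants who do not return the swab and then withdraw or cannot be reached are omitted with no exception for safety data

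*Protocol article*

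**What the plan says.** Five parts of the protocol article bear on this point.

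- **Follow-up (under Trial process).** "Each person will receive a follow-up phone call after the test has been completed". In that call the participant is asked: "Did you experience an adverse event during or after collecting the swab sample". The Minimum data requirements section also lists adverse event details under follow-up information.
- **Timeline.** The trigger is sample return: "After participants return the test samples, they will receive a follow-up phone call".
- **Consent.** One accepted way of leaving the study is "not sending the rectal swab, and then withdrawing after we check in with them after the rectal swab was not returned".
- **Missing data.** After withdrawal following consent, "the reason for withdrawal will be recorded and taken into account in data analysis and interpretation stages". If the swab does not come back, "that participant will be contacted to check if they wish to withdraw from the study", and those who wish to stay are helped to supply it. The section closes with: "If the participant withdraws from the study, or is unable to be contacted, the participant’s data will be omitted".
- **Use of the safety data.** Secondary outcomes (under Statistical methods) counts participants with at least one adverse event and tabulates severity. Objectives of interim analysis includes a safety review. Decision rules gives, as an example of a safety stopping criterion, "if the incidence of severe adverse events is above what is expected".

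**The concern.** Pain or bleeding from the swab is a natural reason to stop, not post the swab, and withdraw. Risks and harm names both as swab risks, and the severity classification gives intense pain and bleeding as examples of severe events. Yet the described question is reached through completing the test and returning the samples, and those who fall out before that point can be omitted. Omission is then related to the outcome being counted.

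At stake is the safety half of the case for replacing bulk faeces with swabs. The reported adverse event percentage could be too low, and the interim safety review could work from a severe event incidence that lacks some of the most relevant cases.

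**Working it through.** The article gives no adverse event rate, withdrawal rate or severe event threshold, so there is no stated figure to reproduce. The check is first textual, then illustrative.

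**Following one participant through the text**

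1. The participant inserts the swab at home, has pain or bleeding, stops, and does not send it.
2. Under Follow-up and Timeline, the adverse event call comes after test completion and sample return. The swab test was not completed, so nothing in those sections guarantees the call.
3. Under Missing data and Consent, there is a check-in about the missing swab. Its stated purpose is to learn whether the person wants to withdraw. No adverse event question is described for it.
4. If the person withdraws, a reason is recorded. If the person cannot be reached, nothing more is learned.
5. In both cases the omission sentence applies and states no exception for safety data. The person therefore enters neither the adverse event count in Secondary outcomes nor the severe event incidence in Decision rules.
6. The recorded reason is to be taken into account in analysis and interpretation, but no section turns it into a counted adverse event.

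**Direction**

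Let p be the true rate among those who attempted a swab, w the share of affected participants omitted, and u the share of unaffected participants omitted.

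Observed rate = p(1−w) / [p(1−w) + (1−p)(1−u)]

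Equivalently, observed odds = true odds × (1−w)/(1−u). The observed rate is too low exactly when w > u. If w were smaller than u, it would be too high.

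**Illustrative size (all inputs assumed)**

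Take u = 5%, p = 1%, 2% or 5%, and w = 25%, 50% or 75%. For 100 people who attempted a swab, the chance that at least one event is seen is 1 − [1 − p(1−w)]^100. With nothing omitted it is 1 − (1−p)^100.

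Worked case, p = 2% and w = 50%:

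- Observed rate: 0.02 × 0.50 / (0.02 × 0.50 + 0.98 × 0.95) = 0.010 / 0.941 = 1.1%.
- Chance of at least one event seen: 1 − 0.99^100 = 63%, against 1 − 0.98^100 = 87%.

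| True rate | Observed rate at w = 25% / 50% / 75% | Chance of ≥1 event seen in 100, nothing omitted | Same chance at w = 25% / 50% / 75% |
|---|---|---|---|
| 1% | 0.8% / 0.5% / 0.3% | 63% | 53% / 39% / 22% |
| 2% | 1.6% / 1.1% / 0.5% | 87% | 78% / 63% / 39% |
| 5% | 4.0% / 2.7% / 1.4% | 99% | 98% / 92% / 72% |

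One hundred is used because interim review is planned at every 100 recruited, or yearly if sooner. The table shows what the rule could do, not what it will do.

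**The case against.** The strongest reply is that the article is condensed and leaves other routes open.

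- **The withdrawal reason is recorded.** Harm may well be the reason given, so it need not vanish from the record. This stands. A reader might infer that the check-in asks only about withdrawal, but the text does not say so. What remains is that a reason noted for interpretation is not a counted, graded adverse event, and an unreachable participant gives no reason.
- **Other routes exist.** The interim review looks at adverse event reports without restricting their source, coordinators stay available to participants, and some swabs are collected with a clinician present. A participant who sends only the faeces sample might still be called. This also stands, and it rules out any claim that such harms can never reach the committee. None of these routes, however, is exempted from the omission sentence.
- **The omission sentence belongs to the text on non-returned swabs.** A reader might infer that it also erases completed pairs, because Consent allows opting out until the analysis. The sentence is unqualified, but it closes a run of sentences about unreturned swabs. Its reach to completed pairs is therefore ambiguous, not established.
- **The two statements in Missing data can coexist.** They can if omission means removal from the paired accuracy analysis while the reason is kept. That is a sensible reading, but the article does not state it.
- **Safety sets and call scripts belong in the full protocol or analysis plan.** This is true of missing detail. Here the article fixes a rule, omission without a safety exception, and that rule is what needs changing.

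**Conclusion.** The point holds for participants who attempt the swab, do not return it, and then withdraw or cannot be contacted. As written, they need not be asked the adverse event question, and they are left out of the adverse event numbers and the severe event incidence. The bias is downward provided affected participants are omitted more often than unaffected ones. That is plausible but is not shown by any figure in the article.

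The size is unknown, and every figure in the table rests on assumed rates. Nor can an effect on a stopping decision be shown: severe event incidence is given as an example without a numeric threshold, and the steering committee's decision is to be multifactorial. The article does not support saying that all swab harms among withdrawers are lost, or that completed pairs are certainly deleted. The second needs clarifying. The change is worth making because it alters a stated rule that can bias the safety result, and it is cheap.

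**What to change.** 1. **Consent and Missing data.** At the check-in already planned for an unreturned swab, ask whether a swab was attempted and, if so, put the adverse event question from Follow-up.
2. **Missing data.** Limit the omission sentence to the paired accuracy analysis. State that adverse events and withdrawal reasons recorded up to withdrawal stay in the safety summaries and the interim safety review, as far as consent allows. State also what happens to a completed pair when the participant later withdraws.
3. **Secondary outcomes and Decision rules.** Base the safety summaries and the severe event incidence on everyone known to have attempted a swab. Report separately the number whose adverse event status is unknown.

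The cost is protocol wording, two questions in a contact already planned, and a small ethics and information-sheet amendment saying that safety data collected before withdrawal are kept. People who cannot be reached will still have unknown status. The change makes that number visible but does not remove it.
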